### Outcome assessment

Participants will be assessed at baseline and the four, 12, and 24 week follow-up sessions by an assessor blinded to group allocation. The physiotherapists, participants and investigators will be asked to avoid giving information which may reveal group allocation to the blinded assessor. Assessor blinding will be checked after each follow-up assessment. The assessor will be asked if he/she was unblinded and will guess the allocation of each participant.

Demographic information will be collected and an X-ray assessment will be carried out by the blinded assessor at the baseline assessment. The X-ray assessment will determine the angle at which the fractured ankle was immobilised and the number of malleoli involved, in order to investigate the relationships between the angle of immobilisation and fracture severity with outcome.

The primary outcomes will be activity limitation and quality of life. They will be measured by the Lower Extremity Functional Scale [42] and the Assessment of Quality of Life scale [43], respectively. On the Lower Extremity Functional Scale, participants will rate the difficulty they have in performing 20 activities on a five-point scale from zero (extreme difficulty or unable to perform activity) to four (no difficulty). The maximum score is 80 points and a higher score denotes less limitation in activity. When tested in a sample of participants with lower limb injuries that included ankle fracture, the scale showed high internal consistency (alpha = 0.96) and test-retest reliability (intraclass correlation coefficient = 0.86), and correlated well with the physical component of the Short Form 36 [42]. The Lower Extremity Functional Scale is capable of discriminating between patients requiring walking aides and patients not requiring walking aides, and has moderate correlations with weight-bearing status and ankle movement [44].

The Assessment of Quality of Life is designed to measure health-related quality of life, and has 15 questions covering five dimensions: illness, independent living, social relationships, physical senses and psychological wellbeing [43]. It has high internal consistency (alpha = 0.81) [43]. The Assessment of Quality of Life is sensitive to changes in health states and is highly correlated with other commonly-used quality of life scales [46]. Population norms have been calculated for the Australian population [46].

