The incremental cost-effectiveness (utility) ratio (ICER) will be calculated as: ICER = (C_E _- C_C_)/(U_E _- U_C_), where C is average cost, U is the average effectiveness or utility score, and subscripts E and C denote the treatment and control arms. Joint mobilisation can be said to be cost-effective relative to exercise alone if it produces less perceived disability and/or greater utility at a lower cost, or the cost per disability avoided or per quality of life gained (i.e., the ICER) is less than some threshold value (e.g., $50,000 in Australian dollars). Sensitivity analysis will be undertaken to explore the robustness and validity of the results. That is, both costs and outcomes will be varied in line with results from similar studies reported in the literature and the upper and lower bounds of the results from this trial.

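### The ICER decision rule carries no condition that mobilisation works better, so read literally it gives the wrong verdict whenever mobilisation works worse

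*Protocol article*

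**What the plan says.** All of this is in the protocol article, mainly in the economic paragraphs that close the Statistical analysis section.

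- The ICER is the difference in average cost (treatment minus control) divided by the difference in average effectiveness or utility. No sign is required of either difference.
- Mobilisation can be called cost-effective by either of two routes. The first is "if it produces less perceived disability and/or greater utility at a lower cost". The second is a test on the cost of each unit of disability avoided or quality of life gained, put as "i.e., the ICER) is less than some threshold value (e.g., $50,000 in Australian dollars". The threshold is thus only an example, and it carries no unit of effect.
- Robustness is to be examined by a sensitivity analysis: "both costs and outcomes will be varied in line with results from similar studies reported in the literature". The same variation is planned over the upper and lower limits of what this trial finds.
- Outcome assessment says of the Lower Extremity Functional Scale that "a higher score denotes less limitation in activity". A negative effect difference on that scale therefore means that mobilisation did worse.

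**The concern.** A ratio of two differences does not say where on the cost-effect plane a result lies. A treatment that is cheaper and better and one that is dearer and worse both have a negative ratio, and both fall below any positive threshold. When the treatment is cheaper but worse, the ratio is the saving per unit of health given up, so a small value is unfavourable. The printed test treats it as favourable.

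Cost-effectiveness is part of the trial's primary aim, so the rule decides a headline conclusion. The unfavourable region is also reachable. Under Interventions the treatment arm is scheduled for 2 x 4 = 8 sessions and the control arm for 2 + 1 + 1 + 1 = 5, which points to extra cost during the intervention period. The sample size was set on the Lower Extremity Functional Scale, so an estimated utility difference on either side of zero is plausible.

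There are two further weaknesses. The first route joins the two outcomes by and/or, so it does not say what the verdict is when they disagree. The second route compares a point estimate with the threshold and attaches no interval or probability to the comparison.

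**Working it through.** The plan gives no cost difference, utility difference or ICER to reproduce. The check applies its formula and test to each part of the cost-effect plane.

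**Inputs.** From the document: the ICER formula, the AUD 50,000 example threshold and 45 participants per group. Assumed: every cost difference, utility difference, standard deviation and standard error below. It is also assumed that the threshold applies per unit of utility (per QALY), since the article states no unit.

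**Formulas.** Let dC be the cost difference and dU the utility difference, treatment minus control. ICER = dC/dU. Net benefit = 50,000 x dU - dC, and a positive value favours mobilisation.

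**Algebra.** If dU > 0, then dC/dU < 50,000 is the same as net benefit > 0. If dU < 0, multiplying through by dU reverses the sign, so dC/dU < 50,000 is the same as net benefit < 0. In the half of the plane where mobilisation is worse, the literal test passes exactly the results it should reject.

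**Numbers.**

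| Mobilisation is | dC (AUD) | dU | ICER | Below 50,000? | Net benefit (AUD) |
|---|---|---|---|---|---|
| costlier, better | +300 | +0.02 | 15,000 | yes | +700 |
| costlier, slightly better | +300 | +0.004 | 75,000 | no | -100 |
| cheaper, better | -300 | +0.02 | -15,000 | yes | +1,300 |
| costlier, worse | +300 | -0.02 | -15,000 | yes | -1,300 |
| cheaper, worse | -300 | -0.02 | 15,000 | yes | -700 |
| cheaper, slightly worse | -300 | -0.004 | 75,000 | no | +100 |

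The first three rows agree with net benefit and the last three contradict it.

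**How often the literal rule would pass.** Take no true utility effect, a fixed extra cost of AUD 200 and a standard error of 0.03 for dU. The break-even gain is 200/50,000 = 0.004. Then P(pass) = P(dU < 0) + P(dU > 0.004) = 0.500 + 0.447 = 0.947, while P(net benefit > 0) = 0.447. Over extra costs of AUD 100 to 500 and standard errors of 0.02 to 0.05, the literal rule passes in 81% to 98% of trials, and net benefit is positive in 31% to 48%.

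A simulation let cost vary as well: 45 per arm, cost SD AUD 400, mean extra cost AUD 150 or 300, utility SD 0.1 or 0.2, no true utility effect. The literal rule passed in 89% to 97% of trials. Requiring dU > 0 brought this down to 39% to 47%, within 0.1 percentage point of net benefit.

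**The sensitivity analysis.** With an extra cost of AUD 200 and dU = 0 with bounds of 1.96 x 0.03 = 0.0588 either side, the ICER is 200/0.0588, about +3,400, at the upper bound and about -3,400 at the lower. Both are below 50,000. At dU = 0 the ratio is undefined. Net benefit runs from 50,000 x 0.0588 - 200 = +AUD 2,740 to -50,000 x 0.0588 - 200 = -AUD 3,140. The ratio looks robust although mobilisation is dominated at the lower bound.

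**The case against.** The strongest reply is that the second route tests a cost per disability avoided or quality of life gained. If mobilisation is worse, nothing has been avoided or gained, and the route does not apply. The structure supports this: a cheaper and better treatment has its own first route, which would be redundant if negative ratios were meant to pass the second. On this reading the dominated case drops out and the threshold test agrees with net benefit. As evidence of intent this stands. It does not fully repair the rule, because the article equates the phrase with the unrestricted ratio and writes no condition that the effect difference be positive. It also leaves cheaper-but-worse results without a verdict.

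A reader might infer that the plan would declare mobilisation cost-effective in about 95% of trials with no true utility effect. The documents do not support that. The excess over 45% comes from the half of results that the words avoided and gained appear to exclude, and the costs and standard error are assumed.

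A reader might also infer that sampling uncertainty is ignored. It is not: the sensitivity analysis covers the trial's own upper and lower bounds. The absence of a named bootstrap or acceptability curve is no fault in itself, since an article may leave such detail to a fuller plan.

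Two smaller objections have force. And/or may simply span the two planned analyses, and nothing says that a worsening in one outcome would go unreported. Extra sessions are scheduled only for the first four weeks, discharge is left open and costs are followed to 24 weeks, so a positive cost difference is plausible but not established.

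**Conclusion.** The decision rule is wrong as written, and the fault is modest. Because the sign of the effect difference is unrestricted, the literal test passes a costlier and worse treatment and reverses the correct inequality for a cheaper and worse one. This follows from algebra and needs no assumed figures beyond a positive threshold. On the more generous reading only the cheaper-but-worse quadrant is left without a rule. In the settings simulated, which all assume extra cost, that gap changes the pass rate by no more than 0.1 percentage point. It would matter more if mobilisation turned out to save money.

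On uncertainty the point is narrower. Bound-by-bound variation does not capture the joint sampling distribution of cost and effect, and it can suggest robustness where the sign of the effect is in doubt. This is an improvement to make, since the plan does address uncertainty.

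No estimate or test of clinical effect is touched. The rule should be corrected before the economic analysis, but it does not threaten the trial.

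**What to change.** 1. For the cost-utility analysis, base the verdict on incremental net monetary benefit at the stated threshold: 50,000 x QALY difference - cost difference > 0. State the unit of the threshold. Give a 95% confidence interval from a bootstrap that resamples each participant's cost and outcome as a pair.
2. Report the ICER, as a cost per unit gained, only where mobilisation is both costlier and more effective. Otherwise describe the result in words, stating dominance where it applies.
3. Replace and/or with separate verdicts for the Lower Extremity Functional Scale and the Assessment of Quality of Life. The AUD 50,000 figure should not be carried over to scale points without justification.
4. Keep the literature-based variation of costs and outcomes as a secondary sensitivity analysis.

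If only one change is made, add the condition that the effect difference must be positive before the threshold test applies, and say how cheaper-but-worse results will be judged. The cost is a few sentences and a small amount of extra analysis work, with no new data.

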## Discussion

The primary aim of this randomised controlled trial is to determine the effectiveness and cost-effectiveness of passive joint mobilisation, in addition to an exercise programme, in adults after cast immobilisation for ankle fracture. The trial incorporates design features known to minimise bias [62]. Participants will be assigned to treatment or control groups using a concealed random procedure. Assessments will be blinded. Data analysis will also be blinded and by intention to treat.

Blinding confers several potential benefits to the rigor of randomised controlled trials, particularly minimising bias [61,62]. Failure to implement blinding could lead to inflated estimates of effects [62,63]. The nature of the treatments involved in this trial means that blinding of the physiotherapists and participants is not possible. Nevertheless, satisfaction with physiotherapy will be evaluated as a means to assess participants' perception of the treatment received.

A pragmatic trial design has been chosen as it can directly inform clinical practice [64, 65, 66, 67]. The inclusion criteria of the trial reflect the variety in patient presentations that would be encountered by physiotherapists in the clinical setting. The experimental protocol also simulates clinical practice. Participants will be treated with the same frequency and for the same duration as would be normal practice, and one form of treatment (joint mobilisation plus exercise) will be compared to another form of treatment (exercise only), instead of placebo. The outcome measures chosen are clinically oriented and participants will be analysed according to group allocation regardless of compliance. Using a pragmatic design broadens the generalisability of the results. An added advantage to this trial is that the pragmatic design allows a realistic economic evaluation of the two treatment alternatives [65].

It is anticipated that data acquisition will finish by early 2007. Results from this trial will contribute to evidence-based guidelines for rehabilitation after ankle fracture.
